## Intervention

We have designed two educational interventions:

*Intervention A: Written information about inhalation techniques* We will give a leaflet of instructions containing pictures and describing the correct inhalation techniques for the main inhaler devices that can be found in our area: Handihaler, Turbuhaler, Accuhaler and pMDI. The patients included in this group will be asked to show how they use their inhalers and the interviewer will write down the mistakes in a template. When the inhalation technique has been performed, the interviewer will give the leaflet to patients and will invite them to read it and to identify differences between the steps of the correct inhalation technique (leaflet) and the one they have performed.

In the follow-up visits we will ask the patients about the difference between the correct way of performing the inhalation technique shown on the leaflet and how they have been using their inhaler.

*Intervention B: Written information about inhalation techniques and instructor training*. We will give written information about the inhalation technique to the patient (leaflet described above) and we will train the patient in the correct inhalation techniques. The training of instructors in the use of inhaler devices has been carried out at the Pediatrics Pneumology Service of Hospital MaternoInfantil (Málaga). We will perform training in three steps:
– Patients will be asked to show how they use their inhalers, using a variety of placebo inhalers.– When the patient has given the demonstration, the trainer will ask about the problems and self-perceived mistakes with the technique.– The trainer will demonstrate the correct technique. Each device will be used and its technique will be explained step by step. The importance of following the correct technique every time the patient uses the inhaler device will be emphasized.Finally the patients can ask questions and they will practice the techniques until they do it correctly or until the patient becomes tired.

In the follow-up visits, we will review the inhalation technique and we will correct any mistakes or clear up any doubt as explained previously. The objective here is that the patients identify their own mistakes, and if they cannot, to remind them of the proper technique by giving as many demonstrations as necessary.

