### Outcomes

*Primary outcome*: Performance of correct inhalation technique. This will be measured using a template designed following SEPAR (Sociedad Española de Neumología y CirugíaTorácica) guidelines [16] where the interviewer will write down any mistakes. It will be considered a good technique when there are no mistakes registered in the template.

*Secondary outcome:* Participants will be evaluated using inhaler peak flow, functional status (spirometry), mental-cognitive status (mini-mental state examination), dyspnea with the Baseline Dyspnea Index (BDI) [28] and Modified Medical Research Council (MMRC) scale [29]; questionnaires on quality of life (St George’s Respiratory Questionnaire [30], and EuroQoL-5D [31]) and the clinical progress of illness (SeguiEPOC questionnaire) will be recorded.

*Independent* v*ariables:* Independent variables will be: sex, age, educational level, smoking history, comorbidity, COPD severity grade (according to GOLD guidelines [24]), prescribed medication, type and number of devices, family support (Family Apgar Test [32]), and social support (DUKE-UNC Test [33]).

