#### Intervention B group:

Inclusion Visit: all the study data will be recorded and the inhalation technique will be tested.

Visit 1 will take place 3 months after the inclusion visit. Primary and secondary outcomes will be measured (excluding spirometry and quality of life) and encouraging correct inhalation techniques using the leaflet and the training with the monitor focusing on motivational aspects to enhance the individual skills of the patients will be individually applied.Visit 2 will take place 6 months after the inclusion visit. Primary and secondary outcomes will be measured (excluding spirometry and quality of life) and encouraging correct inhalation techniques using the leaflet and the training with the monitor focusing on motivational aspects to enhance the individual skills of the patients will be individually applied.Visit 3 will take place 12 months after the inclusion visit. All the study data will be recorded and encouraging correct inhalation techniques using the leaflet and the training with the monitor focusing on motivational aspects to enhance the individual skills of the patients will be individually applied.

A patient will be considered as being lost to follow-up if:
– The patient has not attended two follow-up visits– The patient has declined to continue in the study– The devices considered in the study have been withdrawn

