## Study limitations

One limitation of this study is the selection bias due to the missing data. In order to decrease this bias, we will apply several strategies:
An increase of 40% in the sample size (expected losses)Three phone calls on different days and times for unreachable patientsRescue appointments for the non-attendees to visits (three different appointment dates)In addition we take into account the possible contamination between the control and the intervention groups because of the relationship between subjects in their daily life (neighborhoods, relatives, social networks or associations). However, in another educational intervention study performed with obese patients in our area we did not find a significant level of this effect [35]. We also believe that the intervention characteristics (several steps and individual visits) that we have described will have little influence on contamination between groups.

In order to standardize interventions they will be performed by two professionals trained in communication, the knowledge of disease, and inhalation techniques of the different inhaler devices. Furthermore, we have designed a manual for the researchers where we explain the working plan, the different parts of the intervention, and the protocol in order that they know what they have to measure each time and the details to assess each variable included in the study. In this way, the procedure can be replicated elsewhere.

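### The role that scores the zero-mistake primary outcome also delivers the intervention, explicitly at first contact in arm A and by implication at follow-up, and no masked or separate scorer is described

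*Protocol article*

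**What the plan says.** **Outcome.** The Outcomes section measures technique with a template "where the interviewer will write down any mistakes". The threshold is absolute: "It will be considered a good technique when there are no mistakes registered in the template".

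**Arm A, first contact.** The Intervention section says that "the interviewer will write down the mistakes in a template" and continues: "When the inhalation technique has been performed, the interviewer will give the leaflet to patients". One role scores and then delivers.

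**Arm B, follow-up.** Review and correction appear as one activity of the study team: "In the follow-up visits, we will review the inhalation technique and we will correct any mistakes or clear up any doubt as explained previously".

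**Visit schedule.** The Follow-up section measures the primary outcome at 3, 6 and 12 months. In arm A the same visits include encouragement with the leaflet. In arm B they include "encouraging correct inhalation techniques using the leaflet and the training with the monitor".

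**Control arm.** The Recruitment section has the interviewer score the patient and correct only agreed critical mistakes. It also says that visit length depends on the arm and that the first technique score is taken after randomization.

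**Staff and safeguards.** To standardize the interventions, Study limitations says "they will be performed by two professionals trained in communication" and cites a manual for the researchers. That section discusses missing data and contamination but not assessor bias.

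**The concern.** Whoever follows these arm-specific visit scripts knows the arm, and at follow-up may be judging the result of their own teaching. The outcome is exposed to this. Table 1 lists many steps per device, and some of them, such as emptying the lungs or inhaling slowly, are matters of judgement. For a patient with a single remaining mistake, leaving it unrecorded turns a failure into a success.

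If scoring is more lenient in the taught arms, part or all of an observed difference could be an artefact. Neither the intention-to-treat analysis nor the logistic regression in the Statistical Analysis section can repair an outcome that was misclassified when it was recorded. The template, staff training and manual make the procedure uniform but do not hide the arm.

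**Working it through.** **1. The plan's own sample size.** The Sample size section gives a 25% difference, 80% power, 95% confidence, 40% losses and a total of 296. It states no control rate. I assume 25% correct, because the Discussion reports up to 75% incorrect in the group's previous study. I read the difference as 25 points and the test as two-sided.

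- n per arm = [1.96·√(2·0.375·0.625) + 0.84·√(0.25·0.75 + 0.5·0.5)]² / 0.25² = 57.7, so 58.
- With 40% loss: 58/0.6 = 96.7, so 97 per arm and 291 in total, 1.7% below 296.

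The figure is reproduced closely, conditional on the assumed rate. For the scoring check I use 296/3 ≈ 98 per arm with no loss and 98 × 0.6 ≈ 59 per arm after 40% loss.

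**2. Scoring model.** Let p be the true correct rate, equal in both arms (no true effect). Let f be the share of truly incorrect intervention patients whose every remaining mistake goes unrecorded, with f = 0 in controls. Then

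- observed intervention rate q = p + f(1 − p)
- false difference d = f(1 − p)

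The documents give no value for f, so it is an assumption.

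**3. Worked case: p = 0.25, f = 0.10, 59 per arm.**

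- d = 0.10 × 0.75 = 0.075; q = 0.325; pooled rate 0.2875.
- Null SE = √(2·0.2875·0.7125/59) = 0.0833.
- Actual SE = √[(0.25·0.75 + 0.325·0.675)/59] = 0.0830.
- P(significant in favour) = 1 − Φ[(1.96·0.0833 − 0.075)/0.0830] = 1 − Φ(1.06) = 0.144.
- P(significant against) = Φ[(−1.96·0.0833 − 0.075)/0.0830] = 0.002.
- Two-sided rejection rate = 14.6%, against 5% nominal.

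**4. Range** (pooled two-proportion z-test, two-sided 5%, per comparison with control).

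| True rate p | Share missed f | False difference | Rejection, 59 per arm | Rejection, 98 per arm |
|---|---|---|---|---|
| 25% | 5% | 3.75 points | 7.4% | 9.1% |
| 25% | 10% | 7.5 points | 14.6% | 21.2% |
| 25% | 20% | 15 points | 41% | 61% |
| 8.3% | 10% | 9.2 points | 32% | 48% |
| 40% | 10% | 6 points | 10% | 13.5% |

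The 8.3% is the every-step-correct rate among COPD patients cited in the Background. The 40% is an assumed upper value.

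**5. Leniency that would create the whole target.** f = 0.25/(1 − p): one third at p = 25%, and 27% at p = 8.3%.

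**The case against.** Much of the case on the other side stands.

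- **Who scores at follow-up.** A reader might infer that the document has the arm B trainer score their own patients. It does not say so. The arm A sentence concerns the first contact, where the score precedes the leaflet. The Recruitment section puts follow-up scoring in the passive, and the arm B teacher is called a trainer or monitor, while the scorer is called an interviewer. The overlap at follow-up is an inference, though a strong one, because measurement and teaching share each visit and no other scorer appears.
- **Condensed article.** The researcher manual, which is not shown, may say who assesses what. But this is more than silence: the published workflow itself gives scoring and leaflet delivery to one role.
- **Direction.** A reader might take a bias towards A and B as certain. The stated aim of arm B follow-up is to find and correct mistakes, and a scorer working that way could be stricter.
- **Size.** The rejection rates are not estimates for this trial. The shares missed have no source, and leniency in controls is set to zero. A single missed mistake changes the result only for patients with exactly one. Table 1 marks several common mistakes per device, so many patients may have more.

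**Conclusion.** The point holds as a design weakness that is cheap to improve. The plan gives scoring and delivery to one role, explicitly at first contact in arm A and by strong implication at follow-up in A and B. It describes no masking of the score, and its stated safeguards do not supply any. With a zero-mistake threshold on an observer's judgement, differential scoring could bias the only primary outcome, plausibly but not certainly in favour of the interventions.

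The size depends on the assumed share missed: minor at 5%, material at 10%, and large at 20%. These figures also assume a 25% true rate, no leniency in controls and no true effect. They show how sensitive the comparison is, not that the trial has this bias.

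**What to change.** Add a rule for the 12-month visit, identical in all three arms:

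- The demonstration is scored first, before any leaflet, training or arm-specific record is opened.
- The scorer is an existing trained interviewer or professional who did not teach that patient.
- The patient is asked beforehand not to say what they received.
- Any teaching follows only after the score has been recorded.

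The sample size, the visit schedule and the content of the interventions are unchanged, and no new assessor is needed.

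The change is not free. Staff must be swapped between patients or centres for the 12-month visits, with scheduling and possibly travel across seven centres; the article does not say whether both professionals attend each centre. Masking will be imperfect, since patients may reveal their arm. Scores at 3 and 6 months stay unmasked unless the same rule is applied there.

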### Recruitment

Patients who meet the requirements described above will be contacted using their health center records. They will be invited to participate in the study after a brief explanation by telephone, and they will receive an appointment in the health center. At this first appointment (inclusion visit) patients will receive more detailed information about the study and if they agree to participate, they will sign the written consent.

At this point, they will be divided into three study groups: Intervention A, Intervention B and a control (Figure 1). The randomization will be made using the block randomization technique and applied separately at each study center. The blocks consist of six patients, two subjects per arm; or three patients, one subject per arm (Intervention A, Intervention B and control). The blocks will be marked with a number and they will be chosen at random to create the allocation sequence using a series of random numbers generated by a Microsoft Excel 2003 program. The person responsible for assigning patients to this group will make contact by phone. Because the patients will be from various health centers, the presence of the two interventions and control subjects in all the health centers will be guaranteed.

After randomization, all the study data will be recorded and the performance of correct inhalation techniques will be measured in all groups (inclusion visit). In the case of the control group, the inhalation techniques will be tested by asking patients about how they used their inhalers and the interviewer will write down the mistakes in the template. The interviewer will only correct the critical mistakes previously agreed by the research team and all interviewers who participate in the study. In the follow-up visits the subjects will be invited to perform the inhalation technique and the mistakes will be written down. The appointments last approximately 20–30 minutes, depending on the study arm.

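### Baseline technique is recorded after allocation and, as written, by asking in control but by demonstration in A and B, so it is not comparable between arms; the follow-up test is not distorted by this alone

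*Protocol article*

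**What the plan says.** The Recruitment section of the protocol article sets the order. Patients consent at the inclusion visit and are then allocated: "At this point, they will be divided into three study groups: Intervention A, Intervention B and a control". Data collection follows: "After randomization, all the study data will be recorded and the performance of correct inhalation techniques will be measured in all groups (inclusion visit").

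The baseline procedure is then described by arm.

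- **Control (Recruitment):** "In the case of the control group, the inhalation techniques will be tested by asking patients about how they used their inhalers". The interviewer writes down the mistakes and corrects only those agreed beforehand as critical.
- **Intervention A (Intervention):** patients "will be asked to show how they use their inhalers and the interviewer will write down the mistakes in a template". The same interviewer then hands over the leaflet.
- **Intervention B (Intervention):** "Patients will be asked to show how they use their inhalers, using a variety of placebo inhalers". This is the first step of the training session. The text does not say who fills in the template.

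For follow-up, the control paragraph of Recruitment has subjects perform the technique. Under Outcomes, technique is good only if the template shows no mistake. Statistical Analysis plans a baseline comparison of all groups by chi-square or ANOVA, and pairwise chi-square tests for the primary outcome. On staffing, Study limitations says of the interventions that "they will be performed by two professionals trained in communication". No separate or masked assessor is described.

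**The concern.** A baseline is useful in a randomized trial because allocation cannot have influenced it. Here it is taken once the arm is set. In two arms the scorer's next action depends on the arm, so the scorer evidently knows it. The instrument is an observer checklist on which one recorded mistake turns success into failure, so small differences in strictness or method matter.

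The method also appears to differ by arm. A patient who describes a technique and a patient who is watched performing it need not get the same score. The control arm would further switch method between baseline (asking) and follow-up (performing), while A and B would be assessed by demonstration at baseline.

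At stake are three uses of the baseline: the comparability test in Statistical Analysis, any change or baseline-adjusted analysis, and the Discussion's hypothesis, which concerns patients who were misusing their inhalers at the start. If misuse is identified differently in control, that subgroup is not the same kind of patient in each arm.

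**Working it through.** **1. The plan's own figure.** Sample size gives 296 patients, a 25% difference, 80% power, 95% confidence and 40% losses, but no control rate. I take 25% correct, from the Discussion's statement that up to 75% performed incorrectly. This is an assumption, as are a two-sided test and reading 25% as percentage points.

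- n per arm = [1.96·√(2·0.375·0.625) + 0.84·√(0.25·0.75 + 0.50·0.50)]² / 0.25² = 57.7, so 58.
- Allowing for losses: 58 / 0.6 = 96.7, so 97 per arm. Three arms: 291, close to 296.

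A true rate of 25% is thus compatible with the stated size. Nothing below changes that size.

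**2. Numbers per arm.** Allocation is 1:1:1. At baseline 296 / 3 = 98.7, taken as 98. Evaluable at follow-up: 296 × 0.6 / 3 = 59.2, taken as 59.

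**3. Effect on the baseline test.** Let the true baseline be 25% in every arm, and let asking shift the recorded control rate by s points. The values of s are assumed, because the article gives none. As a simplification I compare control with one intervention arm:

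P(flag) = Φ[(|s| − 1.96·SE₀) / SE₁], with SE₀ = √(2·p̄(1−p̄)/98) and SE₁ = √(p₁(1−p₁)/98 + p₂(1−p₂)/98).

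- Example, s = +10: p̄ = 0.30, SE₀ = 0.0655, SE₁ = 0.0651, so Φ[(0.10 − 0.1283)/0.0651] = Φ(−0.435) = 33%.
- Example, s = −10: p̄ = 0.20, SE₀ = 0.0571, SE₁ = 0.0567, so Φ[(0.10 − 0.1120)/0.0567] = Φ(−0.21) = 42%.

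**4. Effect on a change score.** Let the true 12-month rates be 25% in control and 50% in an intervention arm. Control change = 25 − (25 + s) = −s. Intervention change = 50 − 25 = 25. Difference in change = 25 + s.

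| Shift s in control | False imbalance flagged | Difference in change (true 25) | 12-month difference |
|---|---|---|---|
| +5 | 12% | 30 | 25 |
| +10 | 33% | 35 | 25 |
| +15 | 61% | 40 | 25 |
| +20 | 84% | 45 | 25 |
| −5 | 13% | 20 | 25 |
| −10 | 42% | 15 | 25 |
| −15 | 79% | 10 | 25 |
| −20 | 98% | 5 | 25 |

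**5. Effect on the misuser group.** The recorded share of control misusers is 75 − s. At s = +20 it is 55%, against 75% in A and B.

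**6. The follow-up comparison.** The last column of the table does not move, because follow-up is by performance. Scoring with knowledge of the arm is a separate route. With 59 per arm, no true effect and an assumed scoring shift of 5, 10 or 15 points from 25%, the same formula with 59 in place of 98 gives a significant result about 9%, 22% or 41% of the time, instead of 5%.

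**The case against.** The strongest reply is that the planned primary test never uses the baseline. Statistical Analysis names between-group chi-square tests and no change-from-baseline analysis, and baseline technique is not among the independent variables listed under Outcomes for the logistic model. This stands, and it limits the point.

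A second reply is that asking may be loose wording. The sentence on timing speaks of performance measured in all groups, Follow-up uses the same words for every arm's inclusion visit, and some steps in Table 1, such as inhalation force and actuation timing, can hardly be scored without watching. Study limitations also mentions a manual on how to assess each variable. This stands in part: the difference may not occur in practice. But the control sentence is marked as specific to that arm, and the same paragraph uses a different verb for follow-up. The two sections need reconciling either way, and the timing after randomization is not ambiguous.

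Third, the scorer's knowledge of the arm is an inference. It is well supported for A and control and weaker for B. The two professionals deliver the interventions; the article does not say that they are also the interviewers.

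Three stronger readings are tempting and are not supported:

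- A reader might take the Background figures, 98% who said they knew how to use their device against 8.3% who performed every step, as the gap between asking and watching. They compare declared knowledge with performance. Control patients' mistakes are recorded by an interviewer on a template, so these figures do not measure this gap.
- A reader might infer a spurious advantage as large as the 25-point design effect. That needs one particular assumed shift and a change analysis that the plan does not name.
- A reader might infer that B patients are tested on more devices than their own. The placebo inhalers belong to the training step and may simply cover the prescribed types.

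**Conclusion.** The point holds in a limited form. The article records baseline technique after allocation, with scorers who act by arm in A and control, and it describes different baseline procedures for control and for A and B. As written, baseline technique cannot be compared between arms. A flagged imbalance could not be told apart from chance, and a change score would carry the method difference.

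The size is unknown. Under assumed shifts of 5 to 20 points from a true 25%, with about 98 per arm, a false imbalance is flagged about 12% to 84% of the time if asking overstates correct technique, and somewhat more often if it understates it. A change score is off by the same 5 to 20 points, in the direction of the shift. The 12-month between-arm difference is untouched by the baseline method; only arm-aware scoring at follow-up could bias it, and its extent is not known either. This is an inexpensive improvement to a weak baseline, and it does not show that the primary comparison is invalid.

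**What to change.** 1. Record all baseline data, including technique, after consent and before the allocation call.
2. Reconcile Recruitment with Intervention. In every arm and at every visit, the patient demonstrates the prescribed device type or types, and this is scored on the same template before any teaching or correction.
3. Where existing staff allow, have follow-up technique scored by a team member who did not instruct that patient. This reduces the influence of the arm but does not mask it fully, since patients may reveal what they received. State who fills in the template in arm B.

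The cost is the reordering of one visit, a change to the researchers' manual and some scheduling at follow-up. The sample size does not change.
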